### Patient's inclusion criteria

To be eligible for inclusion in the study, all patients must have regularly visited the same dentist at least once a year for ROEs over the preceding three years. For the MIM arm, patients should also be between 17 and 35 years of age, and with disease-free impacted mandibular third molars in retention.

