### Patient's exclusion criteria

For the ROE arm, patients with symptomatic-driven (emergency) attendance in dental practice, or regular attendance in the participating dental practice of less than three years, are excluded from the study. For the MIM arm, patients with symptomatic or previously removed third molars, or regular attendance in the participating dental practice of less than three years, are excluded from the study

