### Outcomes and instruments

#### ROE study

Table 3 lists the outcome parameters and instruments used. For the ROE arm, the primary outcome measure is the use and appropriateness of individualised risk assessment measured through the assigned recall intervals (in months). The appropriateness will be assessed as follows:

**Table 3 T3:** Outcome parameters and instruments

**Outcome parameter**		**Instruments**
**Primary ROE-outcomes**	Clinical Performance/decision-making: Number of patients per GDP with assigned recall interval (months) based on individual risk profile assessment. For high-risk children and adolescents' intervals less than seven months, in case of low risk profile more than seven months; for low-risk adults' profiles, nine months equal or more, and for high-risk adults' profiles less than nine months.	**Patient record, registration form, to analyse risk management**
**Secondary ROE-outcomes**	Clinical Performance/decision-making: Number of patients per GDP with prescribed individual frequency of BWs (months). For high-risk children and adolescents, frequencies of less than 24 months, and for low-risk profiles, frequencies of more than 36 months; for high-risk adults, prescription frequencies less than 36 months, and for low risk adults, prescription of more than 48 months. Number of patients per GDP with periodontal DPSI-score > 1, and prevalent caries, who have been given feedback, information and preventive advice, registered in patient record or registration form. Efficacy data/cost-effectiveness scores: Mean overall length in months of recall intervals per GDP over the past 3 yrs Mean total number of BW(s) and other radiographs over past 3 years Type of performer GDP/Oral hygienist/others (level of graduation, education) Total number of additional interventions performed during ROE (polishing, removal of calculus: coded as M50, M55). Professional attitudes and compliance: Measured at the beginning and end of the trial, by questionnaire.	**Patient record, registration form, questionnaire to analyse additional performance and cost-analysis**
**Primary MIM-outcome**	Clinical performance/decision-making: Number of patients (between 17 -35 yr of age) with removed versus retained MIMs in accordance with CPG, or with indication for removal. Number of risk-based assessment radiographs between 17– 35-yrs/per patient with risk-based for assessment of prognosis MIM.	**Patient record, registration form to analyse risk management**

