#### MIM study

For the MIM arm, the primary outcome is the use and appropriateness of individualised MIM risk management. The appropriateness will be assessed as follows:

• Patients (17–35 years of age) with removed versus retained MIMs over the past five years as a proportion of patients aged between 17–35 years of age per practice

• Radiographs used for monitoring patients mentioned above to perform a risk-based assessment and prognosis of MIM over the past five years.

A secondary outcome measure is GDPs- attitudes and compliance concerning the recommendations of the MIM-CPG, and relating that information to patients. This measure will use data from patient interviews to confirm risk-based performance.

All data will be collected using special registration forms to be completed by GDPs and patient records available in practices. Questionnaires, patients' records, and registration forms will provide information to assess all outcome parameters. The structured registration forms were used in a previous self-recording study [23].

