### Sample size

The primary outcome measures in this study are collected from individual patients who are clustered within GDPs. GDPs are clustered within (existing) IQual groups which have been randomised to one of the two arms of the trial. The power calculation assumes that the primary outcomes are dichotomous measures, although some outcomes might be treated as continuous measures as well. On the basis of previous research and experience with IQual groups, we expect a relatively high clustering of scores within GDPs, for instance, the intra-cluster coefficient (ICC) for recall interval assignment was 0.29 [23], and a low clustering of scores within IQUAL groups (changing professional behaviour is largely determined by other factors). We use the ICC for clustering in IQual groups, because this was the unit of randomisation. We aim for a 20% change on primary outcomes (e.g. 20 to 40% patients receive individualised recall intervals). Assuming *a power of *80%, alpha = 0.05 and an effect size of 20% for both interventions and an estimated ICC of 0.03 based on previous estimates [21,22], the (Aberdeen) power calculation [24] revealed that six IQual groups (60 GDPs) should comprise 150 registrations (patients) per group, resulting in at least 450 registrations in each trial arm.

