### Statistical analysis

The primary analysis will be performed on an intention-to-treat-analysis. Secondly, measures will be constructed in particular algorithms to define the appropriateness in variables. Thirdly, the impact on each of the primary and secondary outcomes will be estimated separately, using random effects regression models (linear or logistic) to take into account the clustering of data. These basic models include group allocation (intervention, control), measurement timing (baseline, post-intervention), and interaction of group allocation and measurement timing (=intervention effect). Fourthly, prognostic factors for the outcome (which may be confounders) will be added to the models, like patients' recall interval preferences, which varies from those assigned by GDPs, as well as the preferences regarding the prescription of radiographs by patients/GDPs. In addition, this also accounts for GDPs and patients' preferences regarding removal versus retention of asymptomatic impacted third molars. Fifthly, a limited number of subgroup analyses will be performed, including an analysis of effectiveness in participants which performed all activities as planned, i.e., education session, online training program, and helpdesk (= efficacy analysis).

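### The MIM primary outcome has two conflicting definitions, and the one in the text carries no guideline or indication criterion, so it can miss a real gain in appropriate decisions

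*Protocol article*

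**What the plan says.** The MIM study section states that "the primary outcome is the use and appropriateness of individualised MIM risk management". It then lists two measures of appropriateness. The first is "removed versus retained MIMs over the past five years as a proportion of patients aged between" 17 and 35 "years of age per practice". The second concerns radiographs used for risk-based assessment and prognosis.

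Table 3, under Outcomes and instruments, gives the first component of the same primary outcome as the number of patients aged 17 to 35 "with removed versus retained MIMs in accordance with CPG, or with indication for removal".

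Four other places bear on the point:

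- The inclusion criteria restrict MIM patients to those "with disease-free impacted mandibular third molars in retention".
- The exclusion criteria for the MIM arm remove "patients with symptomatic or previously removed third molars".
- The Sample size section treats primary outcomes as dichotomous and collected from individual patients, and states: "We aim for a 20% change on primary outcomes".
- The Statistical analysis section says that "measures will be constructed in particular algorithms to define the appropriateness in variables".

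**The concern.** The trial asks whether implementing a guideline improves decisions about third molars. The outcome therefore has to separate decisions that follow the guideline from those that do not. Table 3 does this. The first measure in the text does not: it records only whether molars were removed or retained. It does not even fix which of the two is the numerator.

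For the ROE outcome, table and text both score decisions against risk-specific rules. Only the MIM text omits the criterion. Because it says how appropriateness will be assessed, an analyst could follow either definition in good faith and reach different conclusions on one of the trial's two main questions. The choice could also be made after the data are seen.

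**Working it through.** **The two definitions side by side**

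| Element | MIM study text, first measure | Table 3 |
|---|---|---|
| Criterion | removed or retained | agreement with CPG, or indication for removal |
| Denominator | patients aged 17–35, per practice | none; a number of patients |
| Window | past five years | none stated |

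**The plan's own figure.** Inputs from Sample size: 20% versus 40%, alpha 0.05 (taken as two-sided), power 80%, ICC 0.03, 150 registrations per group, three groups per arm.

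- The pooled-variance formula for two proportions gives 82 patients per arm.
- Design effect: 1 + (150 − 1) × 0.03 = 5.47.
- 82 × 5.47 = 448.5 per arm, against the stated 450.

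The sample size reproduces for a dichotomous patient-level outcome. The problem is the definition, not the arithmetic.

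**Can the text measure miss a real gain?** Illustration, all counts assumed: 100 patients aged 17–35, of whom 40 have an asymptomatic MIM and 10 of those 40 have a CPG indication for removal.

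- Before: 5 indicated and 5 non-indicated removals. Crude removal is 10/100 = 10%. Concordant decisions are 5 indicated removals plus 30 − 5 = 25 non-indicated retentions, so 30/40 = 75%.
- After: 10 indicated and 0 non-indicated removals. Crude removal is 10/100 = 10%. Concordance is (10 + 30)/40 = 100%.

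Limiting the denominator to the 40 changes nothing: crude removal is 10/40 = 25% both times.

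**General form.** Let q be the share of eligible patients with an indication, a the removal rate if indicated and b the removal rate if not.

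- Crude removal: R = qa + (1 − q)b
- Concordance: A = qa + (1 − q)(1 − b)

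A rises by 20 points with R unchanged whenever q × (change in a) = +0.10 and (1 − q) × (change in b) = −0.10. At q = 0.5, a rises 20 points and b falls 20; at q = 0.3, a rises 33 and b falls 14. The blind spot needs no special value of q.

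**Denominator, literal reading only.** If a share s of patients aged 17–35 has an eligible MIM (not given, so assumed), a 20% versus 40% contrast among them becomes 20s% versus 40s%. Power below uses 450/5.47 = 82.3 effective patients per arm and the same ICC.

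| s | Contrast | Power |
|---|---|---|
| 100% | 20% vs 40% | 81% |
| 75% | 15% vs 30% | 64% |
| 50% | 10% vs 20% | 43% |
| 25% | 5% vs 10% | 23% |

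**Window.** Counting removals over a look-back sits badly with excluding patients whose third molars were previously removed. The intervention starts in months 2–3 and follow-up data are collected in months 8–10. If the five-year look-back also applies at follow-up, only 5 to 8 of its 60 months (8% to 13%) come after the intervention.

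**The case against.** The strongest reply is that the guideline criterion is in the article. Table 3 is presented as the list of outcome parameters, the MIM study section calls the outcome appropriateness, the Statistical analysis section promises algorithms, and the economic evaluation counts guideline adherence among the trial outcomes. Table and text might be complementary, with the criterion in one and the window and unit in the other. This makes the Table 3 concept the likely intent. It does not settle the matter: the text measure is stated without the criterion, and the sentence on algorithms is generic and reconciles nothing.

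Other objections limit how far the point goes:

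- **Dilution.** A reader might infer that the effect will certainly be diluted. The text does not say all patients aged 17–35, and the eligibility criteria may restrict the denominator to registered eligible patients. In that case there is no dilution.
- **A blanket fall in removals.** A reader might infer that only the crude measure would reward it. A uniform fall from 40% to 20% changes concordance by 0.20 × (1 − 2q). At the illustration's q = 10/40 = 0.25, concordance rises from 55% to 65%, so the Table 3 criterion would improve too. Concordance falls only if q exceeds 0.5 (46% to 38% at q = 0.7), and nothing in the article supports such a share.
- **The whole outcome.** A reader might infer that the MIM section cannot show appropriateness at all. Its second measure, on radiographs, addresses risk-based assessment directly and is not affected.

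**Conclusion.** The point holds as a conflict between two definitions of one primary outcome. They differ in criterion, denominator and window, and the article does not say which governs. Followed as written, the text measure cannot separate indicated from non-indicated removals. A 25-point gain in concordance (75% to 100%) can therefore appear as no change (10% and 10%). Those counts are assumed, but the result holds across values of q and under either denominator.

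The loss of power to between 23% and 64% is conditional on the literal denominator and on assumed shares of 25% to 75%. The documents do not support saying that dilution will occur, that the two definitions will give opposite results, or that the trial as a whole measures only how often molars are removed. The stated 450 per arm is reproduced and is not in question here.

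**What to change.** Reconcile the MIM study section and Table 3 into one patient-level definition:

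- **Criterion:** management in accordance with the CPG, as in Table 3.
- **Denominator:** patients who meet the MIM inclusion criteria.
- **Window:** one stated observation period, compatible with the exclusion of previously removed third molars.
- **Other measures:** report crude removal as descriptive only, and keep the radiograph measure.
- **Missing indications:** score a removal with no recorded indication and a retention with no recorded indication separately against the CPG. A single rule that fails every record without a noted indication would misclassify correctly retained molars.

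This adopts the article's own criterion and uses the patient records and registration forms that Table 3 already names. It leaves the stated sample size unchanged if the planned 20% to 40% change is meant for concordance. The cost is some extra scoring work, and the result will depend on how completely indications are recorded, which the article does not establish.

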### Data collection

After their informed consent to participate, GDPs will be invited to first complete a questionnaire to collect personal and practice characteristics, as well as aspects of attitude and compliance. Individual assessment of electronic patient records with regard to the outcome measures, combined with a special registration form (to be applied individually in daily practice), will be used during the evaluation period.

Baseline information will be collected before randomisation of groups, as well as at the end of the trial after seven to nine months. Each GDP will be instructed to complete at least 20 forms per registration period. As each peer group consists of at least eight participants, and each arm will consist of three groups, this will result in a minimum of 480 registrations per trial arm. Finally, questionnaires will be collected from GDPs, dentist's assistants and co-workers to assess acceptance and applicability.

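### The MIM primary outcome rests on two separately estimated measures; nothing says which one decides, and the radiograph measure has no success direction

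*Protocol article*

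**What the plan says.** The MIM study section of the Protocol article names one primary outcome for this arm: whether risk management of impacted third molars is individualised and appropriate. It then assesses that outcome by two bullets. The first is removed versus retained molars over five years, as a proportion of patients aged 17 to 35 per practice. The second is "Radiographs used for monitoring patients mentioned above to perform a risk-based assessment and prognosis of MIM over the past five years".

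Table 3 repeats the pair in its primary MIM row. There, removal/retention is counted against accordance with the guideline or an indication for removal, and the second entry begins "Number of risk-based assessment radiographs".

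The Statistical analysis section says that "the impact on each of the primary and secondary outcomes will be estimated separately". Before that step it promises algorithms that will define appropriateness in the variables. The Sample size section gives "alpha = 0.05 and an effect size of 20% for both interventions", treats the primary outcomes as dichotomous, and remarks that some could also be handled as continuous.

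**The concern.** Two results will be produced under one primary label, and the text does not say whether one, either or both settle the MIM comparison. The radiograph measure adds to the difficulty because it has no threshold and no stated direction. More films could be read as better monitoring of retained molars, and fewer as more selective imaging. The ROE recall outcome has explicit cut-offs by age and risk, and so does bitewing frequency, which is only secondary.

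At stake is what a positive MIM result would mean. The programme could be declared effective because radiograph numbers moved, in whichever direction, while removal decisions stayed the same. If the two measures disagreed, the choice of which to believe would be made after seeing the data.

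**Working it through.** **Inputs.** From Sample size: power 80%, alpha 0.05 (sidedness not stated), "We aim for a 20% change on primary outcomes (e.g. 20 to 40% patients receive individualised recall intervals", and "an estimated ICC of 0.03 based on previous estimates". From Data collection: "each arm will consist of three groups". The stated result is 150 registrations per group and at least 450 per arm. The documents give no MIM rates and no correlation between the two MIM measures, so the correlations below are assumptions.

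**Step 1: reproduce the plan's figure.**
- Individually randomised, two-sided 0.05, pooled variance under the null, no continuity correction: n = [1.96·√(2·0.30·0.70) + 0.842·√(0.20·0.80 + 0.40·0.60)]² / 0.20² ≈ 81.2, so 82 per arm.
- With three groups of size m per arm, 3m = 82·[1 + (m − 1)·0.03]. Hence m = 82·0.97 / (3 − 82·0.03) = 79.54 / 0.54 = 147.3 per group, or 442 per arm. This is within 2% of 150 and 450.
- Variants that do not fit: one-sided, 57 per group; one-sided with continuity correction, 92; two-sided with continuity correction, 327.

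The stated size therefore matches one dichotomous test at the full two-sided 0.05. There is no allowance for a second primary measure and no calculation for a number of radiographs per patient.

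**Step 2: nominal power at the planned size.** Design effect = 1 + 149·0.03 = 5.47. Effective n per arm = 450 / 5.47 = 82.3. Power is 80.5% at alpha 0.05 and 71.6% at alpha 0.025.

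**Step 3: what each possible rule would imply for two measures.**

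| Rule | Chance of a false MIM claim | Power |
|---|---|---|
| Either suffices, each at 0.05, independent | 1 − 0.95² = 9.75% | depends on both effects |
| Same, correlation 0.5 | 9.1% | as above |
| Same, correlation 0.8 | 7.8% | as above |
| Either suffices, each at 0.025, independent | 1 − 0.975² = 4.94% | 71.6% per measure |
| Both required, each at 0.05 | at most 5% | 0.805² ≈ 65% if independent |
| One named measure at 0.05 | 5% | 80.5% |

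The correlated rows use 1 − P(|Z₁| < 1.96 and |Z₂| < 1.96) for a bivariate normal pair. The rate falls to 5% as the correlation approaches 1. The power figures for two measures assume that radiographs would have the same nominal power as the dichotomous outcome, which the plan does not show.

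**The case against.** The strongest reply is that the protocol names a single MIM primary outcome, and Table 3 uses the singular heading for it. The promised algorithms might code both bullets into one appropriateness variable. Rules on multiplicity commonly sit in a statistical analysis plan, which is not shown here. The Sample size section also admits that some outcomes may be continuous.

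Much of this stands. A reader might infer that each measure is tested at full alpha, that either one suffices, and so that the MIM false-positive rate is nearly double 5%. The documents do not say so. Alpha appears only in the sample-size calculation, and no either-one-wins rule is written. The two measures come from the same patients and clusters, so some correlation is plausible. The 9.75% is therefore conditional. The absence of an alpha split is not in itself a finding.

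Two further inferences also fail. One is that the ROE primary belongs in the same family of tests; ROE and MIM are separate clinical questions, which the Study design section treats as largely independent. The other is that fewer removals with more films would necessarily be contradictory. Retaining teeth and monitoring them can be one coherent pattern, and that section says this arm's intervention covers monitoring as well as the removal decision.

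The reply does not remove the definitional gap. The shown text itself places two measures under the primary label, has outcomes estimated separately, and leaves one measure without a criterion. The algorithms are described only as defining appropriateness, not as choosing between or combining the two measures.

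**Conclusion.** The point holds as a badly fixed primary outcome. Two different measures serve as the MIM primary, the text shown does not say which decides, and radiographs have no cut-off or direction. That conclusion depends on no assumed correlation.

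The size is conditional. The ceiling of 9.75% requires that either measure counts as success at 0.05 and that the tests are independent. Requiring both keeps the rate at or below 5% but costs about 15 points of nominal power (80.5% to about 65%), under independence and equal power. Splitting alpha costs about 9 points per measure (80.5% to 71.6%). All power figures take the plan's ICC, rates and normal approximation as given. The Discussion already concedes that the study may be underpowered, so naming one deciding measure is the least costly repair.

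**What to change.** 1. Reconcile the definition of removal/retention first. The MIM study section gives a five-year proportion per practice with no benchmark, while Table 3 counts accordance with the guideline or an indication for removal. The outcome needs one definition and one stated direction of success, used in both places.
2. In the MIM study section and Table 3, name that measure as the single deciding MIM primary, tested at two-sided 0.05.
3. Make radiographs secondary, reported with an estimate and confidence interval, or test them only if the primary is significant.
4. State that ROE and MIM are separate questions, each with one primary test.

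This is a change of wording and needs no further patients or data. It holds the MIM error rate at 5% and keeps the plan's nominal power. The cost is that a change in radiographs alone can no longer support a claim that the MIM programme is effective.
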